### Randomization, allocation, and blinding

The randomization procedure employed in this study adhered to rigorous standards, utilizing a randomized number table method. Subjects were allocated randomly into three groups (control group, fixed reward group and probabilistic reward group) at a precise ratio of 1:1:1, ensuring that each group consisted of 27 participants. Group allocation was meticulously executed using the sealed envelope method. Prior to participant assignment, random allocation sequences were meticulously generated and securely housed within sequentially coded, sealed, opaque envelopes. Following confirmation of subject eligibility by the researcher, envelopes were systematically unsealed, and subjects were then allocated to their respective groups.

In adherence to stringent confidentiality protocols, prior to envelope unsealing, the names and comprehensive profiles of eligible subjects were meticulously transcribed onto the exterior of each envelope. Duplicate records were also securely enclosed within, serving as a safeguard against any potential data loss or discrepancies. Furthermore, to ensure the utmost confidentiality and integrity of the allocation process, each envelope was reinforced with an additional layer of protection, such as a hardboard or tin foil insert, effectively shielding its contents from visibility under intense lighting conditions.

To uphold the scientific rigor of the study and mitigate the risk of bias, a single-blinding approach was meticulously implemented. This method ensured that assessors remained blinded to the subjects’ group allocations and the specific intervention protocols administered. Moreover, to maintain consistency and objectivity in the evaluation process, all patient training sessions and subsequent assessments were meticulously recorded. These assessments were conducted by therapists who were intentionally kept unaware of the patients’ group assignments. In case of anomalous data detected during data analysis or data verification, the designated data analyst will promptly notify both the principal investigator and the assessor. Subsequently, a comprehensive review of the recorded sessions will be conducted to verify the accuracy and reliability of the obtained results, thereby upholding the highest standards of scientific integrity and validity.

### Intervention

Following the completion of the informed consent process, participants will formally commence the trial protocol. Throughout the inpatient period, hand motor function rehabilitation training will be administered once daily, with each session lasting approximately 20 min. This regimen comprises three Pegboard Tests and three BBT. In the context of the pegboard test, a common assessment tool used in rehabilitation settings, motor performance is evaluated by measuring the time it takes for individuals to complete specific tasks involving moving pegs from one location to another on a pegboard. The pegboard test often varies in complexity, with tasks ranging from simple movements to more challenging ones requiring precise coordination and dexterity. The Pegboard Test will be stratified into three difficulty tiers based on training complexity: peg removal, peg insertion, and peg flipping, further classified into three levels according to peg size.

The training regimen encompasses two distinct phases. In phase one, known as the baseline assessment, the Pegboard Test evaluates the maximum difficulty level of actions that patients can successfully complete and identifies the minimum peg size. BBT training entails patients transferring blocks as swiftly as possible within a 1-min timeframe, with a 1-min inter-session rest period, during which the number of successfully transferred blocks is recorded.

Phase two entails rehabilitation training, wherein patients undergo hand motor training once daily for 10 consecutive days, employing the highest difficulty level of actions and pegs. Patients are tasked with completing all pegs expeditiously. Following each training session, there will be a 1-min rest period, after which the pegboard will be reset for three additional pegboard training sessions. Patient metrics, including maximum action difficulty, peg size, and completion time, will be meticulously documented. BBT training will adhere to the same protocol as the baseline assessment, recording the number of successfully transferred blocks within a 1-min duration, repeated thrice.

Participants assigned to the control group will complete the training regimen as stipulated, devoid of any reward system. Conversely, participants in the fixed reward group will receive a 5 RMB incentive for each completed test prior to pegboard and box block trials, culminating in a total reward of 30 RMB upon completion of three pegboard tests and three BBT sessions daily. Those allocated to the probabilistic reward group will obtain a lottery opportunity following each completed experiment, entailing monetary rewards ranging from 1, 2, 5, 10, and 15 RMB, with an average probability reward of approximately 5 RMB. Consequently, completing three pegboard tests and three BBT sessions daily may yield rewards ranging from 6 RMB to 90 RMB. We prepared a square paper box to serve as a dark box for drawing lots. There is a total of 70 ping-pong balls inside, with 20 balls labeled with the number 1, 16 balls labeled with the number 2, 16 balls labeled with the number 5, 10 balls labeled with the number 10, and 8 balls labeled with the number 15. The amount of money awarded corresponds to the number marked on the ping-pong ball.

To ensure consistency and quality of the intervention measures throughout the trial, a detailed intervention protocol will be developed outlining the procedures, techniques, and timing for implementing different reward strategies. This protocol will serve as a guide for all interventionists to ensure uniformity in the delivery of interventions. Interventionists will be required to accurately document the delivery of each intervention session using standardized forms. This documentation will include details such as the content of the intervention, duration, participant responses, and any deviations from the protocol. The research team aims at ensure consistency and quality in the delivery of intervention measures. Maintaining intervention fidelity is crucial for accurately evaluating the effectiveness of different reward strategies in improving motor learning ability and rehabilitation motivation among stroke patients.

The safety and well-being of participants will be closely monitored throughout the duration of the study. Adverse events and serious adverse events will be promptly reported to the relevant regulatory authorities and the ethics committee, and appropriate measures will be taken to ensure participant safety.

### Outcome assessment

The components of the assessment include basic information (gender, age, duration of illness, medication history, etc.), motivation, motor performance and objective assessments. The main assessments focus on motivation and motor performance. Comprehensive video recordings of each training session will be subjected to meticulous analysis to evaluate daily motor performance. Rehabilitation motivation evaluations and functional near-infrared spectroscopy (fNIRS) measurements will be conducted at designated time points (Table 1).

**Table 1 tab1:** Recommended content for the schedule of enrolment, interventions, and assessments.

	Study period						
	Enrolment and assessment	Allocation	Training			Follow-up	
Timepoint	−D_1_	0	D_1_	D_2_–D_9_	D_10_	D_14_	D_28_
Enrolment							
Eligibility screen	X						
Informed consent	X						
Allocation		X					
Interventions							
Control group							
Fixed reward group							
Probabilistic reward group							
Assessments							
SRMS	X		X		X	X	X
MAP-SR	X		X		X	X	X
PRPS	X		X		X	X	X
Motor performance	X		X	X	X	X	X
fNIRS	X		X		X	X	X

### Primary outcomes

The Stroke Rehabilitation Motivation Scale (SRMS) is a validated assessment tool developed by Australian scholar White in 2012, specifically tailored to measure the motivation levels of stroke patients engaging in rehabilitation programs (16). It offers a structured approach to evaluate various dimensions of motivation essential for effective rehabilitation. The scale comprises seven dimensions, including amotivation, external regulation, introjected regulation, identified regulation, integrated regulation, intrinsic motivation to know, and intrinsic motivation to accomplish. Each dimension represents different aspects of motivation, ranging from external factors like rewards or obligations to internal factors such as inherent satisfaction and personal goals. It consists of 28 items, including both positively and negatively phrased statements, allowing for a nuanced assessment of motivation levels. The SRMS serves as a valuable tool in rehabilitation practice, enabling clinicians to assess, monitor, and address motivational barriers to maximize the effectiveness of stroke rehabilitation programs.

### Secondary outcomes

The second outcomes include motor performance, STEF, MAP-SR, and PRPS.

Motor performance assessment involves evaluating the ability of individuals to execute motor tasks effectively. This assessment typically encompasses factors such as the level of task difficulty, characteristics of the equipment used (e.g., peg size), and the time taken to complete tasks. The Simple Test for Evaluating Hand Function (STEF) is a valuable assessment tool specifically designed to evaluate hand and upper limb function. Developed initially by Kaneko Tsubasa in Japan and subsequently adapted for use in the United States (17). The STEF provides objective measurements of performance, allowing clinicians to track progress over time and compare results to normative data. The Motivation and Pleasure Scale Self-Report (MAP-SR) is an assessment tool originally developed by Llerena et al. (18). The MAP-SR encompasses items that probe different dimensions of motivation and pleasure, allowing for a comprehensive understanding of an individual’s subjective experiences. The Pittsburgh Rehabilitation Participation Scale (PRPS) is a vital assessment tool developed by [name] EJ at the University of Pittsburgh in 2004 (19). The scale offers a structured and systematic approach to assess the extent to which individuals engage in and contribute to their rehabilitation process during inpatient treatment. The PRPS serves as an indispensable tool for rehabilitation specialists, enabling us to assess, promote, and monitor patient participation in rehabilitation programs.

Functional Near-Infrared Spectroscopy (fNIRS) serves as a valuable tool for assessing brain activity and hemodynamic responses during motor tasks in stroke patients. During the assessment, participants will engage in motor tasks, such as hand function exercises, while fNIRS sensors are placed over predetermined cortical areas. Researchers can quantitatively evaluate the effectiveness of different reward strategies in modulating cortical activation patterns, thus elucidating their impact on motor learning ability and rehabilitation motivation in stroke patients.

Regular quality control checks will be conducted throughout the trial to monitor the consistency and accuracy of assessments. This will involve periodic reviews of assessment videos or live observations by a designated quality control team to identify any discrepancies or issues in assessment administration. Feedback will be provided to assessors, and additional training or clarification will be offered if necessary to rectify any identified issues.

### Data collection and data management

Ensuring the precision and trustworthiness of research data stands as a cornerstone in clinical studies. A methodical process encompassing data collection, verification, locking, and unblinding is meticulously employed to uphold rigorous data quality standards. At the outset, paper-based Case Report Forms (CRFs) and specialized assessment scales are meticulously employed to mitigate potential human errors during data collection. Each CRF undergoes meticulous transcription into the database by two independent personnel, with any disparities promptly rectified using software tools to augment efficiency and establish a resilient data foundation. During the data verification phase, spearheaded by a dedicated data administrator, stringent protocols are enacted to meticulously identify and rectify any errors or inconsistencies in the data entry process. This phase is of paramount importance in ensuring the precision and reliability of the dataset. Subsequent to verification, the data is securely locked to safeguard its integrity and prevent unauthorized alterations without unanimous agreement. This procedure serves to uphold the sanctity and fidelity of the dataset throughout the analysis phase. In the pivotal unblinding process, statistical analysis unveils the treatment modalities received by participants, subsequently followed by the disclosure of treatment group statuses. Transparency and impartiality in this phase are of utmost importance in upholding the scientific integrity and credibility of the trial results.

Overall, this rigorous data collection and management protocol are devised to furnish invaluable insights into the efficacy of diverse reward strategies in stroke rehabilitation. By adhering to exacting data quality standards, the study aspires to contribute significantly to the refinement of rehabilitation protocols tailored for stroke patients.

### Statistical analysis

Categorical variables like gender and affected side will be presented as percentages and compared using the chi-square test. Continuous variables will undergo normality assessment with the Shapiro–Wilk test and variance homogeneity examination with Levene’s test. One-Way ANOVA will compare motivation among groups before and after training, followed by Tukey’s HSD test for *post hoc* comparisons. The repeated measures ANOVA was performed to analyze changes in rehabilitation motivation scales data and average time spent in pegboard test and BBT in the three groups. Non-normal or heterogeneous data will be analyzed using the Kruskal-Wallis test, with *post hoc* tests conducted using Dunn’s test. Normal data will be presented as mean ± standard deviation, while non-normal data will be presented as median and quartiles. The significance level (P) for hypothesis testing will be set at 0.05.

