**Methods:**

A total of 81 stroke patients will be recruited and randomly assigned to control, fixed reward, or probabilistic reward groups at a ratio of 1:1:1 using a randomized number table method. Participants will undergo 10 days of daily hand motor function rehabilitation training, with sessions lasting 20 min each. The training will involve pegboard tests and box and block tests. Control group participants will receive standard training, while fixed reward group members will receive monetary incentives for completing tests, and probabilistic reward group members will have the chance to win monetary rewards through a lottery box. Rehabilitation motivation and motor performance and functional near-infrared spectroscopy brain imaging will be conducted at designated time points. The primary outcome measure is the stroke rehabilitation motivation scale, and the second outcome measures include motor performance, simple test for evaluating hand function, motivation and pleasure scale self-report, and Pittsburgh rehabilitation participation scale.

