### Sample size

The statistical software G-power (Heinrich Heine University Düsseldorf, Dusseldorf, Germany) was utilized to ascertain the sample size, with an alpha value set at 0.05, power at 0.95. By employing Cohen’s d using data extracted from a prior study by Chen et al. (15), we ascertain the mean discrepancy between groups to be 2.34 (27.54–25.2), with a pooled standard deviation approximating 3.47. Acknowledging the discrepancy in sample sizes between the two groups, the effect size is computed to be 0.674. With these parameters, the calculated sample size per group was determined to be 23 participants, summing up to 69 participants across three groups. Anticipating a dropout rate of 15%, the final sample size was adjusted, necessitating 27 participants per group, resulting in a total sample size of 81 participants.

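### Neither of the two planned SRMS analyses uses the pre-allocation score as a covariate, which costs precision and protection against chance imbalance but does not bias the result

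*Protocol article*

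**What the plan says.** The abstract of the protocol article states: "The primary outcome measure is the stroke rehabilitation motivation scale". Under Outcome assessment, "Rehabilitation motivation evaluations and functional near-infrared spectroscopy (fNIRS) measurements will be conducted at designated time points", and Table 1 lists those points for SRMS as -D1 (enrolment, before allocation), D1 (first training day, after allocation), D10, D14 and D28.

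The Statistical analysis section gives SRMS two parametric analyses:

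- "One-Way ANOVA will compare motivation among groups before and after training", followed by Tukey's HSD for the pairwise comparisons. No covariate is named.
- "The repeated measures ANOVA was performed to analyze changes in rehabilitation motivation scales data", applied also to the pegboard and BBT data.

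The fallback is rank-based: "Non-normal or heterogeneous data will be analyzed using the Kruskal-Wallis test", with Dunn's test. It has no covariate either. The section does not say which analysis of SRMS is primary.

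**The concern.** A one-way ANOVA before training tests whether randomised groups differ at baseline. Any such difference is due to chance, so the test answers no question the trial asks, and a non-significant result does not protect the later comparison.

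A one-way ANOVA after training ignores each patient's own starting score, although that score is collected. Whatever part of the post-training variation it would explain stays in the error term. Any chance difference between arms at -D1 also passes, in proportion to the correlation, into the group contrast. The randomisation section mentions no stratification that would limit this.

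The repeated measures ANOVA does use earlier scores, but in its simplest pre/post form it subtracts baseline rather than regressing on it. That is less efficient than covariate adjustment for any correlation below 1. The only parametric pairwise procedure named, Tukey's HSD, is attached to the unadjusted ANOVA. The direct comparison of fixed with probabilistic reward, which is the trial's stated aim, would therefore come from the analysis that makes no use of baseline.

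**Working it through.** **Inputs from the Sample size section.** "the mean discrepancy between groups to be 2.34 (27.54–25.2), with a pooled standard deviation approximating 3.47"; "the effect size is computed to be 0.674"; "with an alpha value set at 0.05, power at 0.95"; 23 evaluable and 27 recruited per group. The section does not say that the mean difference and SD are SRMS values; they serve here as the plan's own effect size.

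**The plan's figures.** 2.34 / 3.47 = 0.674, so the effect size reproduces. The 23 per group does not: a two-sided two-sample t test at 95% power needs 59 per group. That is a separate matter. It is relevant here only because power at 23 per arm starts well below the stated 0.95.

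**Assumed input.** r, the correlation between -D1 and post-training SRMS, is not in the documents. I use 0.3 to 0.8, with equal SDs at the two times.

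**Formulas.** Pairwise two-sided t test at alpha 0.05, error variance pooled over three arms of 23, no Tukey adjustment, noncentrality = d* × √(23/2):

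- Post-only: d* = 0.674, df = 69 − 3 = 66. Noncentrality = 0.674 × 3.391 = 2.29; power 0.615.
- Change score (the repeated measures ANOVA read as a pre/post group-by-time test): error variance 2(1 − r) of the post-only variance, d* = 0.674/√(2(1 − r)), df = 66.
- ANCOVA: error variance 1 − r² of the post-only variance, d* = 0.674/√(1 − r²), df = 65.

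| Assumed r | Variance ratio, change | Variance ratio, ANCOVA | Power, post-only | Power, change | Power, ANCOVA |
|---|---|---|---|---|---|
| 0.3 | 1.40 | 0.91 | 0.615 | 0.478 | 0.656 |
| 0.5 | 1.00 | 0.75 | 0.615 | 0.615 | 0.739 |
| 0.6 | 0.80 | 0.64 | 0.615 | 0.712 | 0.804 |
| 0.7 | 0.60 | 0.51 | 0.615 | 0.829 | 0.884 |
| 0.8 | 0.40 | 0.36 | 0.615 | 0.946 | 0.964 |

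ANCOVA has the highest power in every row. The change score beats the post-only test only when r exceeds 0.5. The ratio of ANCOVA to change-score variance is (1 − r²)/(2(1 − r)) = (1 + r)/2, which is below 1 whenever r is below 1.

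**Chance imbalance.** With 27 per arm, the standard error of a baseline difference between two arms is √(2/27) = 0.272 SD. At r = 0.6, an imbalance of that size moves the post-only contrast by 0.6 × 0.272 = 0.163 SD, and 0.163/0.674 = 24% of the planned effect. The change score over-corrects, moving it by (0.6 − 1) × 0.272 = −0.109 SD. ANCOVA removes the part that is linear in baseline.

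**The case against.** The strongest reply is that the plan does not discard baseline. The sentence after the one-way ANOVA plans a repeated measures ANOVA on the same scales, and at r = 0.7 the gain of ANCOVA over a change score is about 0.06 in power (0.884 against 0.829), far less than the 0.27 over the post-only test (0.884 against 0.615). This stands. A reader might infer that the one-way ANOVA is the primary SRMS analysis and that baseline goes unused; the article labels neither analysis primary, so that inference is not supported.

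A reader might also infer that the unadjusted comparison is biased. It is not. Under randomisation it is unbiased on average and keeps its type I error, and its standard error already includes chance imbalance.

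Third, the size of the gain rests on an assumed r. At r = 0.3, ANCOVA adds only about 0.04 to the post-only power. This also stands, and is why the whole range is shown.

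Finally, covariates are often left to a statistical analysis plan. But the article does not leave the analysis open: it names the models, and neither has a baseline covariate. A repeated measures ANOVA over all five time points would also behave differently from the pre/post reading used above; the article does not say which is meant.

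**Conclusion.** The point holds as a free improvement. SRMS has two stated analyses with neither named primary, neither adjusts for the -D1 score as a covariate, and the pre-training ANOVA serves no inferential purpose. The consequence is lost precision and weaker protection against chance imbalance, not an invalid test.

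On the plan's own effect size with 23 per arm, ANCOVA adds between 0.04 (r = 0.3) and 0.35 (r = 0.8) to the power of the post-only comparison, and between 0.18 (r = 0.3) and 0.02 (r = 0.8) to that of a change score. These figures assume equal SDs at the two times, ignore the Tukey adjustment, and take 0.674 to apply to SRMS, which the article does not state. It would go too far to say that adjustment restores the planned 0.95: among the values checked, ANCOVA reaches it only at r = 0.8.

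**What to change.** In the Statistical analysis section:

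- Make the primary SRMS analysis an ANCOVA of post-training SRMS, at a named time point, on group, with -D1 SRMS as covariate.
- State that baseline means -D1. D1 falls after allocation and could already reflect knowledge of the assigned reward.
- Report Tukey-adjusted pairwise group differences with 95% CIs from that model.
- Describe baseline SRMS by group without a hypothesis test.
- Keep the repeated measures ANOVA and label it supportive.

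The cost is a few sentences and one degree of freedom. No new data or visits are needed, because -D1 SRMS is already scheduled in Table 1.

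### The sole primary outcome (SRMS) is given two unranked analyses at 0.05; if either could carry the primary claim, the false-positive rate for any group difference would exceed 5%

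*Protocol article*

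**What the plan says.** The abstract of the protocol article states: "The primary outcome measure is the stroke rehabilitation motivation scale". The Primary outcomes section describes the scale but attaches no visit, score change, model or contrast to it. Under Outcome assessment, "Rehabilitation motivation evaluations and functional near-infrared spectroscopy (fNIRS) measurements will be conducted at designated time points", and Table 1 marks SRMS at −D1, D1, D10, D14 and D28. D10 is the last training visit; D14 and D28 fall under follow-up.

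The Statistical analysis section gives two analyses of motivation:

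- "One-Way ANOVA will compare motivation among groups before and after training", "followed by Tukey’s HSD test for" the pairwise comparisons.
- "The repeated measures ANOVA was performed to analyze changes in rehabilitation motivation scales data", together with pegboard and Box and Block Test times.

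One level covers everything: "The significance level (P) for hypothesis testing will be set at 0.05". There is also a fallback: "Non-normal or heterogeneous data will be analyzed using the Kruskal-Wallis test". Nothing in the section ranks the two analyses or says which visit or model term decides.

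**The concern.** The two analyses answer different questions. The one-way ANOVA asks whether the groups differ at a visit. The repeated measures ANOVA asks whether they differ on average over visits (group term) or change differently over time (group-by-time term). They can disagree: D10 may be significant next to a null interaction, or the reverse, and the text has no rule for that case. With several unranked routes to a significant SRMS result, 0.05 is the level of each test but not necessarily of the primary claim.

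Tukey's HSD does not close this gap. It controls the three pairs within one ANOVA, not across visits and not across the two analyses. The Kruskal-Wallis fallback changes the test statistic but leaves the deciding visit just as open. The Sample size section does not settle it either, since it works from one two-group difference and names no visit or test.

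**Working it through.** **Inputs from the article.** Three arms of 27 (Randomization section); SRMS at five visits (Table 1); 0.05 per test; one-way ANOVA before and after training; repeated measures ANOVA (Statistical analysis section).

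**Assumptions, not in the article.** Any significant test counts as success; all five visits enter the repeated measures ANOVA; between-visit correlation of 0.3 to 0.8, as compound symmetry or AR(1).

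**Which tests count.** The pre-training one-way ANOVA compares randomised arms before treatment, so it is not a test of effect and is left out. The closest reading of the post-training ANOVA is D10.

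**Rough benchmark.** For k independent tests at 0.05, the chance of at least one false positive is 1 − 0.95^k:

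- k = 2: 1 − 0.9025 = 9.75%
- k = 3: 1 − 0.8574 = 14.3%
- k = 4: 1 − 0.8145 = 18.5%

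The real tests are correlated, so they were simulated.

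**Simulation under no group difference.** 40,000 trials per setting, 27 per arm, five visits, Greenhouse-Geisser correction for the repeated measures interaction. The ranges run over both correlation structures.

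| What counts as success at 0.05 | False-positive rate |
|---|---|
| D10 one-way ANOVA alone | 4.8–5.2% |
| D10, or the group term | 6.8–8.9% |
| D10, or group-by-time | 8.8–9.8% |
| D10, or either term | 11.0–12.6% |
| D10, D14 or D28, or group-by-time | 13.7–16.3% |
| D10, D14 or D28, or either term | 14.0–18.5% |

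The first row reproduces the article's own 0.05, so one named test holds its level. The second and third rows give the 7–10% of the closest reading. The last row is the widest post-training reading. If the correlation is 0.9, the second row falls as low as 6.3% and the last as low as 12.7%.

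**The fixed versus probabilistic contrast.** With three groups and 81 − 3 = 78 degrees of freedom, Tukey's 5% critical value is q = 3.379. As a t statistic this is 3.379/√2 = 2.389, a per-pair two-sided level of 1.9%. Simulated under compound symmetry (20,000 trials per setting), the chance that this contrast is significant at any of D10, D14 or D28 is:

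- correlation 0.3: 5.3%
- correlation 0.5: 5.2%
- correlation 0.7: 4.5%
- correlation 0.9: 3.5%

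So repeated looks over the three visits use up Tukey's margin but barely pass 5%. This covers the one-way ANOVAs only; the article states no pairwise method for the repeated measures ANOVA.

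**The case against.** The strongest reply has four parts.

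- **This belongs in the analysis plan.** Time point, deciding term and testing order are often left to a SAP or full protocol, and neither is shown. Comparing levels and analysing change can also be complementary. That would answer a complaint about silence. But the article is not silent: it prescribes two tests of its only primary outcome at the same level and does not rank them. The fault is in the stated text.
- **No rule says that any significant result wins.** This stands. A reader might infer that the trial's false-positive rate simply is 9% to 18%. The article does not support that: the figure needs a success rule, a set of tests and a correlation that it does not give. The rates are what could happen if nothing is fixed.
- **The one-way ANOVA is not planned at all five visits.** This also stands. It is stated only before and after training, and Table 1 separates D14 and D28 as follow-up. A reader might infer repeated one-way testing across the whole schedule; the text does not say so. The article speaks of analysing changes, which points to group-by-time rather than the group term. The upper range therefore needs a wide reading.
- **The stated aim is fixed versus probabilistic reward.** The Introduction says so, and for that Tukey contrast the rate stays near or below 5%. This stands and limits the finding to the omnibus claim. It does not remove it, because no section names that contrast as primary and the analysis compares all three groups.

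**Conclusion.** The concern holds in a limited form. The article gives its sole primary outcome two unranked analyses at 0.05, with no deciding analysis, visit or term. If a significant result on either counted, the false-positive rate for any group difference on SRMS would be about 7–10% on the closest reading. It could reach about 14–18% only if D14 and D28 also counted as post-training visits and both repeated measures terms counted. Both ranges are conditional on the assumptions listed in the check. Neither is a property that can be read off the plan, and neither applies to the Tukey-adjusted fixed versus probabilistic contrast within the one-way ANOVAs. What does not depend on those assumptions is the absence of a rule for conflicting results. A choice made after unblinding would be open to the charge that the results drove it.

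**What to change.** In the Primary outcomes and Statistical analysis sections, name one primary test of SRMS at 0.05. One suitable choice is the between-group comparison at D10, the end of training, from one named model with Tukey-controlled pairs. State that the repeated measures analysis and all other visits are secondary and cannot support the primary claim if that test fails. If the sponsor prefers the repeated measures analysis as primary, name its visits and the deciding term and make the one-way ANOVA secondary.

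This should be done before unblinding. It is a change of wording and needs no further patients or assessments. In the simulation one named test returns the rate to about 5%. The small downside is that the other routes to a significant primary result are closed.

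### The analysis sentence names average time for the Box and Block Test, whose duration is fixed at one minute, and takes pegboard time forward without the difficulty level at which it was measured

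*Protocol article*

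**What the plan says.** In the protocol article, Statistical analysis covers the motor outcome in one sentence: "The repeated measures ANOVA was performed to analyze changes in rehabilitation motivation scales data", and in the same sentence the "average time spent in pegboard test and BBT in the three groups".

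The Intervention section describes the two tests differently.

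- **BBT.** "BBT training entails patients transferring blocks as swiftly as possible within a 1-min timeframe". The training phase follows the baseline procedure, "recording the number of successfully transferred blocks within a 1-min duration, repeated thrice".
- **Pegboard.** The tasks are "peg removal, peg insertion, and peg flipping, further classified into three levels according to peg size". At baseline, "the Pegboard Test evaluates the maximum difficulty level of actions that patients can successfully complete and identifies the minimum peg size". Training then runs daily for 10 days, "employing the highest difficulty level of actions and pegs". Action difficulty, peg size and completion time are all recorded.

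Secondary outcomes describes motor performance as covering "the level of task difficulty, characteristics of the equipment used (e.g., peg size), and the time taken to complete tasks". Table 1 schedules motor performance at baseline, on every training day, and on days 14 and 28.

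**The concern.** There are two separate problems.

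**BBT.** The sentence names a time, but the test has a fixed time and a variable count. As worded, the BBT variable has no variance.

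**Pegboard.** Three actions by three peg sizes allow up to nine different tasks, and each patient is measured at a personal maximum. The protocol makes difficulty and peg size part of the outcome, yet only seconds reach the analysis. Seconds from a slow task and from a quick task then enter the same average. The article also does not say whether a patient's level is locked at baseline or can move up over the 10 days and the follow-up. If it can move, a patient who improves may be timed on a harder task and show little or no gain.

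Motor learning is one of the two things the trial sets out to compare, and Outcome assessment names motor performance with motivation as the main assessments. An ineffective-looking result could come from the choice of variable rather than from the reward strategy.

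**Working it through.** The plan gives no figure for this outcome, so there is none to reproduce. The check has four steps.

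**1. BBT time.** Inputs from the protocol: 27 patients per group, three groups, one minute per trial. Every value is 60 s, so the between-group and within-group sums of squares are both 0 and F = 0/0 is undefined. A one-way ANOVA on 3 × 27 values of 60 returned no F and no p value.

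**2. Pegboard, level fixed per patient: why seconds lose precision.** Let b be log time at baseline (which includes the level) and c the change in log time. Then

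- change in seconds = exp(b) × (exp(c) − 1)
- change in log time = (b + c) − b = c

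In seconds, the same relative gain counts for more when the task is slow, so the spread of levels adds noise. On the log scale a fixed level cancels.

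**3. Size of the loss.** From the protocol: 27 per group, significance level 0.05. Assumed, not in the document: typical baseline time 60 s; between-patient SD of log time 0.3; mean log change −0.15, −0.25 and −0.35 in the three groups (largest difference 0.2); SD of change 0.2; SD of level 0, 0.3 or 0.6. The test was one-way ANOVA on one change score, 4,000 runs per setting.

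| SD of level (log scale) | Rejection with no effect, seconds | Power, seconds | Power, log time |
|---|---|---|---|
| 0 | 0.044 | 0.83 | 0.91 |
| 0.3 | 0.048 | 0.73 | 0.90 |
| 0.6 | 0.049 | 0.53 | 0.91 |

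The log column agrees with theory. The variance of the group means 0, 0.1 and 0.2 is 0.00667; 0.00667 / 0.2² = 0.1667; noncentrality = 81 × 0.1667 = 13.5. With 2 and 78 degrees of freedom this gives power 0.91.

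**4. Pegboard, level raised for those who improve.** Assumed: a patient whose log change is below −0.25 moves to a task that adds 0.4 to log time; SD of level 0.3. The expected observed change is m + 0.4 × P(c < −0.25):

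- m = −0.15: −0.15 + 0.4 × 0.309 = −0.027
- m = −0.25: −0.25 + 0.4 × 0.500 = −0.050
- m = −0.35: −0.35 + 0.4 × 0.691 = −0.073

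The largest group difference shrinks from 0.200 to 0.047. Simulated power was 0.16 in seconds and 0.18 on the log scale, so the log transform alone does not solve this case.

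**The case against.** **BBT.** The sentence can be read as pegboard time and, separately, the BBT. The block count is plainly the recorded result, and nobody would run an ANOVA on a constant. This is fair: it is probably a slip of wording and no data are lost. But on the looser reading the BBT has no named variable at all, so the sentence needs correcting either way.

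**Pegboard.** A reader might infer that the planned analysis cannot measure motor performance, or that unlike tasks are compared between arms and bias the result. The document does not support that. With a fixed level, each patient's change is measured on the same task. Randomisation makes the baseline level noise rather than bias, and the rejection rate with no effect stayed at 0.044 to 0.049. Block counts are collected too, and STEF is a separate hand-function outcome.

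A reader might also judge the loss from the inflated spread of times at a single visit. That would model the wrong test: the plan analyses change, and on the log scale a fixed level drops out.

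**Level progression.** The natural reading is that training uses the level found at baseline, and recording difficulty again does not show that it moves. A reader might infer that the effect changes sign. That needs progression, which is unstated; even in the scenario above the difference was masked, not reversed.

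**Remedy.** A log scale and covariates are often left to an analysis plan. That is a fair reason to rank the pegboard part lower. It does not excuse an analysis sentence that leaves out components the outcome definition includes.

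**Conclusion.** The concern holds in two parts of unequal weight.

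- **BBT: wrong as written.** Statistical analysis names a time and Intervention fixes that time at one minute. This needs no assumption and should be corrected.
- **Pegboard: a cheap improvement, not an invalid analysis.** With levels fixed per patient, seconds give a valid test of change that loses precision as levels spread: power 0.83 to 0.53, against about 0.90 on the log scale. These figures rest wholly on assumed SDs and effects and on a single change score, whereas the plan has more visits; they show direction and rough size only. The problem becomes serious only if levels rise during the trial (power 0.16 to 0.18 in one assumed scenario), which the article leaves open.

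Motor performance is a secondary outcome. The primary analysis of the Stroke Rehabilitation Motivation Scale is unaffected.

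**What to change.** Replace the motor part of the sentence in Statistical analysis with two variables:

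1. **BBT:** mean number of blocks per minute over the three trials of a session.
2. **Pegboard:** log completion time at the action and peg-size level set at baseline, adjusted for baseline log time and baseline level.

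Add one statement on whether the level stays at its baseline value throughout training and follow-up. If it can change, state in advance how a change is scored, and report level changes separately.

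The cost is a change of wording before the data are analysed: block counts, action difficulty, peg size and completion time are already recorded. Only if levels do progress might there be extra work, namely one timed trial at the baseline level at each assessment, or a scoring rule in its place.
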